## Abstract

**Background:**

Depressive disorders are common mental health problems during adolescence. Many adolescents with depression describe difficulties with sleeping. Findings of previous studies regarding changes in objective sleep quality in adolescents with depressive disorders are heterogeneous.

**Aims:**

This study aims to investigate differences in objective and subjective sleep quality between adolescents with depressive disorders and healthy peers, and to evaluate if potential changes in sleep occur concurrently with changes in the release of cortisol and alpha-amylase after awakening.

**Method:**

This non-interventional parallel study examines correlations between depressive disorders, sleep quality and release of stress hormones. Sleep quality in the past 2 weeks, severity of depressive symptoms, psychiatric comorbidities and stress response of 30 adolescents with depressive disorders and 30 healthy controls (*N* = 60) are assessed via questionnaires. In participants’ home environments, the objective sleep quality of seven consecutive nights is measured by sleep accelerometry. After awakening, participants answer sleep questionnaires to examine the subjective sleep quality of those nights. Furthermore, salivary cortisol and alpha-amylase are measured three times after awakening (+0 min, +30 min and +45 min after awakening).

**Conclusions:**

Sleep is an important factor for prognosis and well-being in adolescents with depression. The results of this study can be highly valuable to integrate a more detailed examination of sleep quality and sleeping impairments in the treatment of adolescent depressive disorders.

## Depression as a global health problem

According to the World Health Organization, depression is the ‘leading course of disability worldwide’ and ‘a major contributor to the overall global burden of disease’, with more than 264 million people of all ages with depressive disorders.^1^ Affecting performance at school or work, as well as relationships and family constellations, depression threatens not only the global living environment of individuals, but of society as a whole.^2^

## Depressive disorders in adolescence

Depressive disorders are common mental health problems during adolescence. In a survey conducted in the USA, a lifetime prevalence of about 12% was found for the adolescent sample, and prevalence nearly doubled from early (13/14 years: 8.4%) to late adolescence (17/18 years: 15.4%).^3^ Additionally, the number of adolescents with depressive symptoms is even higher when considering the high number of adolescents with subthreshold depression, with a lifetime prevalence of up to 20% at the age of 18 years.^4^

Depressive disorders during adolescence are associated with more burdensome circumstances in adulthood, including mental health problems, suicidal ideation or attempts, reduced educational attainment and economic status, lower relationship quality and higher levels of conflicts and violence.^5^ This underlines the importance of a deeper understanding of the aetiology and severity of depressive disorder.

## Sleep disturbance in patients with depressive disorder

Sleep disturbance constitutes an important symptom of depressive disorders, and it gains even greater importance when considering that it may increase the risk of suicidal behaviour among adolescents.^6^ Delayed sleep onset and decreased sleep efficiency, combined with changes in rapid eye movement (e.g. shorter latency and increased activity, density and amount of rapid eye movement sleep) and slow-wave sleep (e.g. decreased sleep amount), are frequent findings from studies assessing sleep in adults with depression.^7^ Regarding paediatric depression, findings are far more heterogeneous. In his review dealing with sleep disturbance in paediatric depression, Rao considered 24 electroencephalogram studies conducted in children and adolescents.^7^ A prolonged sleep latency was found in eight of these studies, and 15 studies found no differences. A decrease in sleep efficiency was found in three of the studies, and 19 studies found no differences.^7^ As sleep underlies multifarious influences in the context of development, the heterogenous study situation could reflect the complexity of sleep quality and its components during the developmental period.^7^ Examination of sleep latency and efficiency via accelerometry, as conducted in this study, has been shown to be a promising approach in previous research.^8,9^

In addition to objective measures of sleep quality, the burden of impaired subjective sleep quality and sleep complaints caused by depression should be considered. Many studies in adults with depressive disorders have assessed subjective sleep quality, and findings show that over 80% of patients report sleep difficulties.^10^ Previous research showed that similar impairments can be found in adolescents with depressive disorders. Considering only subjective sleep assessments without objective sleep data, Gupta et al found impaired sleep quality, delayed sleep onset, shorter sleep duration, and a correlation of sleep quality with severity of depressive symptoms.^11^ These abovementioned impairments in subjective as well as objective sleep quality may lead to serious mental burden and an increased stress level in everyday life for many adolescents with depression; therefore, both measurements are important to consider.

## Cortisol

A hormone that plays a key role in the experience and management of stress is the glucocorticoid hormone cortisol. Its secretion from the adrenal cortex^12^ depends on stimulation by adrenocorticotropin released by the anterior pituitary gland (hypothalamus–pituitary–adrenal (HPA) axis activation), and follows a characteristic diurnal rhythm with a peak in the early morning.^12^ Activation of the HPA axis and the ability to adjust cortisol release is an important contributor for adapting to stressful life events, and providing energy and physical resources to cope with the demanding situation.^13^ Chronic activation, however, is linked to various somatic and mental health problems.^13,14^ In our study, we focus on the strength of the cortisol peak within 45 min after awakening, known as the cortisol awakening response (CAR).^13^ Characteristics of the CAR include a precipitous increase after awakening, a maximum within about 30 min after awakening and a subsequent decline.^12^ CAR constitutes a ‘reliable biological marker for adrenocortical activity’.^15^ An increased as well as a decreased CAR is associated with stress and multifarious health problems, such as autoimmune, allergic and psychiatric illnesses.^13,16^ Several previous studies examined changes in the CAR in differently structured samples of adults with depressive disorders. Bhagwagar et al^17^ observed an increased CAR in adult patients with depressive disorders; Vreeburg et al^18^ found similar results in patients with remitted and current depressive symptoms. Additionally, Stroud et al^16^ examined an interaction between larger CAR and a greater extent of depressive symptoms, whereas Huber et al^19^ found an attenuated CAR in psychotherapy in-patients with depression. In adults with subclinical depressive symptoms, an attenuation of the CAR was found by Mangold et al.^20^ According to Elder et al,^21^ the use of antidepressant medication may be a contributing factor to the inconsistency of findings, and so we include only participants who are not taking antidepressant medications. Regarding our study cohort, previous research with adolescent study samples is of particular interest. In young girls with depressive disorders, Schmidt et al^14^ found a significantly higher CAR. However, this study did not exclude adolescents on antidepressant medications; therefore, our study design with a medication-free sample adds important value to the current study situation.

## Alpha-amylase

Another measurement for the activation of physiological stress systems is the enzyme alpha-amylase. It is secreted by the sympathetic and parasympathetic innervated salivary glands, and constitutes an important biomarker of autonomic nervous system activity with a sensitive responsiveness to acute stress situations.^22^ Examining alpha-amylase levels of adult patients with depression, recent studies found elevated salivary alpha-amylase levels after awakening, and provided evidence that alpha-amylase may be a promising biomarker for depressive disorders.^23^ Regarding paediatric depression, very few studies have examined alpha-amylase levels in children and adolescents with depression.^24^ To our knowledge, no study has focused on the reactivity of alpha-amylase with various measurements after awakening in adolescent patients.

The examination of alpha-amylase provides further information regarding the stress system dysregulation compared with an exclusive assessment of cortisol,^25^ which makes a parallel measurement of these two biomarker a useful approach.

## Interrelation between sleep, depressive symptoms and psychophysiological correlates

When examining the link between sleep quality, depressive symptoms and psychophysiological correlates, the interrelations are multifactorial and the direction is partially unclear. Fang et al found that the association between sleep and depressive symptoms in adult patients with depression is bidirectional, with sleep impairment being a comorbidity as well as a prodromal sign of a depressive disorder.^26^ In adolescent patients, previous studies reported a connection between sleep problems and later depressive symptoms,^27^ but prior research also identified that higher severity of depressive symptoms was associated with poorer sleep quality.^28^

There are also indications that sleep and stress biomarkers are linked bidirectionally. A hyperactivity of the HPA axis can influence sleep architecture and decrease sleep quality, but sleep impairments also negatively affect functioning of the HPA axis.^29^ A previous study observed a positive association between sleep duration and levels of cortisol, but no association between subjective sleep quality and cortisol levels at awakening, whereas levels of alpha-amylase at awakening were not significantly associated with sleep duration, but a worse subjective sleep quality was associated with higher alpha-amylase levels at awakening.^30^

Much research was performed examining the relationship between cortisol and depressive symptoms in adolescents and adults. In this context, the release of cortisol is considered a heritable trait,^31^ with a connection to current^14^ and future^16^ depressive symptoms. Referring to alpha-amylase, prior research found elevated alpha-amylase levels at awakening in adult patients with depression,^23^ but first investigations in an adolescent sample did not confirm this alpha-amylase morning elevation in adolescent patients with depression.^24^

## Implications for the planned study

According to Nater et al, the simultaneous examination of HPA axis indicators (cortisol) and biomarkers of the autonomic nervous system (alpha-amylase) is a recommended approach, providing further information about psychobiological stress responses.^22^ By repeatedly analysing cortisol as well as alpha-amylase levels after awakening in adolescents with depression and healthy controls, we are able to assess neuroendocrinological biomarkers that may play a key role in many depressive symptoms, including sleep impairments. Based on the secretion mechanism and physiological compartment, we do not expect a correlation between cortisol and alpha-amylase secretion.

Additionally, our study design enables us to examine sleep and psychophysiological correlates as close to reality as possible. Examining sleep in participants’ home environments^10^ and the simple and non-invasive wearing of a watch-like accelerometer barely influences participants’ natural sleeping habits,^9^ and makes a realistic assessment of subjective as well as objective sleep quality possible. Together with saliva sampling in a familiar environment,^32^ these ambulatory assessment methods lead to a high ecological validity of the study findings.

## Study aim

Investigating the relationship between sleep quality and depressive symptoms, our study's goal is to compare objective measurements and subjective assessments of sleep quality between adolescents with depressive disorders and healthy peers. Another focus of our study lies in the examination of salivary cortisol and alpha-amylase releasing patterns after awakening as a potentially correlated factor in altered sleeping patterns.

## Hypotheses

We hypothesise that adolescents with depressive disorders will show a lower objective sleep quality with lower sleep efficiency, longer onset latency, more frequent awakenings and longer wakefulness after sleep onset (WASO) than healthy controls. Based on previous studies, we expect the subjective sleep quality of participants with depression to be considerably lower than that of the control group (less satisfaction with sleep, worse mood after awakening, lower feeling of recreation after awakening, impression of frequent awakenings during the night and impaired subjective quality of dreams). Additionally, in accordance with Schmidt et al^14^ and Bauduin et al,^23^ we hypothesise an increased CAR and elevated alpha-amylase levels after awakening in the index group compared with the healthy control group.

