### Outcomes

#### Primary outcome

The primary outcome of our study is the difference between the index group and control group on all measures of subjective (daily self-assessment questionnaires) and objective (ActTrust measurements, sleep onset latency, sleep efficiency, WASO and awakenings) sleep quality, the pattern of the CAR and the course of alpha-amylase after awakening.

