### Statistical analysis

Data will be collected in accordance with the current standard of empirical research. Data will be evaluated with IBM SPSS Statistics version 25.0 for Windows (released 2017; IBM Corp, Armonk, New York). First, depending on the distribution of control variables, differences between the adolescents with depression and the control group will be computed via *t*-tests or Mann–Whitney *U*-tests. As cortisol and alpha-amylase levels are commonly skewed, a square-root transformation will be applied to achieve a normal distribution.^64^ Cortisol and alpha-amylase measurements will be averaged over three days and entered into the repeated measures ANCOVA as the dependent variable, with group as the independent variable.

Cortisol and alpha-amylase increase will be computed by area under the curve analyses.^65^ For an additional measure of increase, delta scores will be computed between baseline and the highest value.^66,67^ To determine group differences in cortisol and alpha-amylase increase, ANCOVAs will be calculated with group as an independent variable.

To examine the relationship between subjective and objective sleep quality, depressive symptoms and cortisol/alpha-amylase increase, bivariate correlations with a false discovery rate correction will be computed.^68^ Effect sizes will be reported with Cohen's *d*, with 0.2 being considered a small, 0.5 a medium and 0.8 a large effect.

Finally, in case of non-normality distributed and sufficiently skewed outcome variables, the direction of the relationship between sleep quality and depressive symptoms will be examined with direction dependence analysis.^63^ Direction dependence analysis enables to statistically test the directional relation between pairs of variables, including observational variables, as well as adjusting for covariates that may contribute to the causal process.^69^

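### The alpha-amylase hypothesis is about level, but the correlations with sleep and symptoms use only its increase, which subtracts the awakening value

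*Protocol article*

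**What the plan says.** Under Hypotheses, the article expects a larger cortisol awakening response, which is a change, and "elevated alpha-amylase levels after awakening in the index group", which is a level.

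The background section on the interrelation of sleep, symptoms and psychophysiological correlates reports that "a worse subjective sleep quality was associated with higher alpha-amylase levels at awakening". The same section describes the adult depression finding as a raised value at awakening, and adds that first work in adolescents did not confirm it.

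Statistical analysis gives both markers the same treatment:

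- Level model: "Cortisol and alpha-amylase measurements will be averaged over three days and entered into the repeated measures ANCOVA as the dependent variable", with group as the factor.
- Index 1: "Cortisol and alpha-amylase increase will be computed by area under the curve analyses".
- Index 2: "delta scores will be computed between baseline and the highest value".
- Group test on the indices: "To determine group differences in cortisol and alpha-amylase increase, ANCOVAs will be calculated with group as an independent variable".
- Relations with sleep and symptoms: for sleep quality, "depressive symptoms and cortisol/alpha-amylase increase, bivariate correlations with a false discovery rate correction will be computed".

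Primary outcome names "the pattern of the CAR and the course of alpha-amylase after awakening". Nowhere is a level index (awakening value, mean, or area under the curve to ground) named for alpha-amylase in the correlations.

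**The concern.** The quantity expected to be altered in depressed adolescents is the amylase level. The quantity correlated with sleep and symptoms is the rise or fall from the awakening sample. If amylase is higher throughout the first 45 minutes in those who sleep worse or are more depressed, the increase carries none of that signal. If it is higher mainly at awakening, where the cited evidence places it, the increase is smaller in those participants and the correlation can point the other way.

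Relating sleep to the biomarkers is a stated focus under Study aim. A null or negative amylase correlation could therefore be reported as evidence against a link that the analysis was not able to see.

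**Working it through.** **Inputs from the article.** Samples at 0, 30 and 45 minutes after awakening; 30 participants per group, 60 in total; alpha 0.05 (taken as two-sided). The article gives no amylase profile, SD or between-sample correlation, so those below are assumptions. There is no stated figure to reproduce.

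**Step 1: the indices (trapezoid rule).** Let y0, y30 and y45 be the three values on the analysis scale.

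- AUC to ground = 15(y0 + y30) + 7.5(y30 + y45) = 15·y0 + 22.5·y30 + 7.5·y45
- AUC increase = AUC to ground − 45·y0 = 22.5(y30 − y0) + 7.5(y45 − y0)
- Delta = highest value − y0

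The last two depend only on differences from y0. Adding the same constant to all three values leaves them unchanged, whatever the shape of the curve.

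**Step 2: illustrative profiles (arbitrary units).**

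| Profile | AUC to ground | AUC increase |
|---|---|---|
| 100/70/75 | 3637.5 | −862.5 |
| 130/100/105 (all +30) | 4987.5 | −862.5 |
| 130/70/75 (awakening only +30) | 4087.5 | −1762.5 |
| 100/130/140 | 5475 | 975 |
| 130/130/140 (awakening only +30) | 5925 | 75 |

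With a raised awakening value, AUC to ground rises and AUC increase falls, for both falling and rising curves.

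**Step 3: effect on a correlation.** Assume SD 1 at each sample and a common between-sample correlation ρ.

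- Variance of AUC increase = (1 − ρ)(30² + 22.5² + 7.5²) = 1462.5(1 − ρ). SD = 27.04 at ρ = 0.5 and 17.10 at ρ = 0.8.
- Variance of AUC to ground = (1 − ρ)(15² + 22.5² + 7.5²) + ρ·45² = 787.5(1 − ρ) + 2025ρ. SD = 37.50 at ρ = 0.5 and 42.16 at ρ = 0.8.

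*Parallel elevation.* Let a sleep or symptom score correlate 0.5 with a person's stable amylase level (variance ρ).

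- With AUC to ground: r = 0.5·45·√ρ / SD = 0.42 at ρ = 0.5 and 0.48 at ρ = 0.8.
- With AUC increase: the weights sum to zero, so r = 0.

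In simulation with 60 participants at an uncorrected 0.05, power was 93–98% for AUC to ground and about 5%, the false-positive rate, for AUC increase.

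*Elevation greatest at awakening.* If the score correlates r0 with the awakening sample and a smaller r1 with both later ones, its correlation with AUC increase is 30(r1 − r0)/SD, which is negative. Each 0.1 by which r0 exceeds r1 contributes −3/27.04 = −0.11 to −3/17.10 = −0.18.

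**Step 4: the same reversal as a group contrast.** Take +0.6 SD at awakening and +0.3 SD later.

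- AUC increase: 30 × (0.3 − 0.6) = −9, so −9/27.04 = −0.33 SD to −9/17.10 = −0.53 SD.
- AUC to ground: 15 × 0.6 + 30 × 0.3 = 18, so 18/37.50 = 0.48 SD to 18/42.16 = 0.43 SD.

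**Step 5: is level tested anywhere?** Yes, for the group comparison. The repeated measures ANCOVA takes the measured values, and its group main effect is a contrast of level. In simulation (30 per group, +0.8 SD at every sample) the three-sample mean had power 0.97 at ρ = 0.5 and 0.90 at ρ = 0.8, against 0.96 and 0.90 for AUC to ground. No stated analysis does the same for sleep or symptoms.

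**The case against.** A reader might infer that the alpha-amylase hypothesis goes untested, or that the group ANCOVAs on increase are the wrong analysis. The documents do not support either reading. The repeated measures ANCOVA tests level through its group main effect, with about the power of AUC to ground, so replacing the increase in the group comparison would gain almost nothing. The increase indices also have a purpose of their own. Primary outcome names the course of amylase, Study aim speaks of releasing patterns, the Alpha-amylase section presents reactivity after awakening as the gap to be filled, and Knowledge gains asks about the strength and course of the awakening responses. They should stay.

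Nor does the article present the awakening association as its reason for measuring amylase. It is one background result, and the article also reports that the morning elevation was not confirmed in adolescents. Sign reversal is thus a possibility, not a prediction. Hypotheses contains no directional sleep–amylase or symptom–amylase statement.

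Two technical replies deserve weight. First, an ANCOVA with the awakening value as covariate would give the same group coefficient for AUC increase as for AUC to ground. The article does not list its covariates, and this cannot help the correlations, which are bivariate. Second, the AUC formula sits behind a citation and may be defined in a fuller plan. But the article itself names the correlated variable as an increase, so this is not a detail merely left open.

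What stands after all this is the correlation analysis.

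**Conclusion.** The point holds for the correlations only. As written, no analysis relates sleep quality or depressive symptoms to alpha-amylase level, although level is what the article hypothesises to be altered and what its cited sleep evidence concerns.

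Cancellation of an elevation that is constant on the analysis scale is exact and needs no assumption about the curve. Reversal is conditional: it arises, for example, when the awakening value is raised most, and the documents do not say whether it is. The sizes above (a correlation of 0.42 to 0.48 reduced to zero; a group contrast of −0.33 to −0.53 SD where the level contrast is +0.43 to +0.48 SD) rest on assumed profiles, equal SDs and between-sample correlations of 0.5 to 0.8. They are illustrative only.

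**What to change.** 1. In the correlations, add one level index for alpha-amylase beside the increase: AUC with respect to ground, or the awakening value. Choose it in advance and put it in the same false discovery rate family.
2. State that the group main effect of the repeated measures ANCOVA tests the hypothesis on amylase level, and that the ANCOVAs on increase address the course after awakening. A raised level together with a smaller increase then has a fixed reading.
3. Keep the increase indices for amylase, and leave cortisol unchanged.

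The same three samples serve, so no new data are needed. The cost is one further test per sleep or symptom measure correlated, and with it a slightly stricter false discovery rate correction for the family.
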